### Interim analyses {21b}

No interim analyses will be conducted due to the low-risk nature of our intervention, and the relatively short period of time in which it is administered.

### Methods for additional analyses (e.g. subgroup analyses) {20b}

Sub-group analysis will be conducted to compare the medication and no-medication groups using the above analysis methods, as a secondary exploration.

The qualitative analysis of peer experiences will be achieved using emergent thematic analysis of verbatim transcript data. Qualitative interviews of peers will take place via Zoom for Healthcare, or in-person in a private room at the University of Calgary (Pandemic guidelines permitting) and will be approximately 1 hour in length. Interviews will be audio recorded and transcribed verbatim, by a certified transcription service. Transcripts will be coded using emergent thematic analysis.

### Methods in analysis to handle protocol non-adherence and any statistical methods to handle missing data {20c}

Analysis will be completed in accordance with an intention-to-treat (ITT) model and will therefore include all participants, regardless of protocol adherence or missing data. A secondary sensitivity analysis will also be conducted including only those who completed the intervention with adherence to the treatment protocol.

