### Eligibility criteria {10}

#### Inclusion and exclusion criteria

English-speaking pregnant participants over the age of 18, who complete the baseline P3 cohort questionnaire, and score >10 on the Edinburgh Postnatal Depression Scale (EPDS), who reside in the Calgary Health Region and are less than 27 weeks’ gestation (to enable completion of the intervention prior to delivery, and allow us to capture the vast majority of preterm deliveries) will be eligible for inclusion. Participants undergoing no current psychotherapy or pharmaceutical treatment, or who have been on a stable dose of anti-depressant medications (e.g. SSRIs) for 3 months or more and score 10 or more on the EPDS will be eligible. We will exclude anyone who has a lifetime diagnosis of severe psychiatric illness (bipolar disorder, schizophrenia, borderline personality disorder, other psychoses) and/or is engaged in an active treatment regimen for a diagnosed mental illness (counselling; non-SSRI medications) at trial intake.

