### Intervention description {11a}

The intervention has been pilot tested with pregnant individuals and is comprised of a BA therapy module, a short workbook, and informal peer support from study entry until 6 weeks postpartum. The intervention will be primarily administered through the secure and encrypted Zoom for Healthcare by trained peer counsellors (below); peer counsellors will also connect with participants over the telephone as needed (e.g. check-ins) or based on barriers to videoconference (e.g. technical issues, no internet or camera). The counselling module is aligned with the BA treatment manual, adapted from the Alma BA peer-mentorship intervention [36], and tailored to reflect the perinatal context [11, 18]. It includes treatment strategies: mapping, problem-solving, scheduling activities, communicating and activating social supports [18]. Treatment will involve an average of 6–8 structured counselling sessions that are flexible and responsive to individual needs. At the conclusion of every counselling session, the peer counsellors will complete the Session Rating Scale, which solicits feedback from the participant about progress and the quality of the therapeutic relationship, and has been shown to improve participant fidelity as well as perceived therapeutic benefit [37–39]. The workbook content compliments the BA treatment strategies and was developed using patient-oriented methods by members of our team. It includes simple activities that serve as complementary tools for activity scheduling, identifying prenatal and anticipating postnatal stressors, and identifying and activating social supports. It also serves as a print resource that can be consulted between sessions and into the postpartum (and beyond), which was a patient-identified preference in pilot research [29]. Completion of the activities is not required to attend the sessions; participants will be guided through the treatment strategies by the peer counsellors during the sessions. The BA therapy will also be supplemented by informal unstructured peer support, including text and telephone contact between participants and peer counsellors from study enrollment through 6-weeks postpartum. Intervention-pilot results showed the intervention and remote delivery is feasible, the content is acceptable and useful to patients, when administered by a psychologist [29]. Qualitative evaluation showed that participants identified improved parenting confidence in the early postpartum and found the intervention helpful with mitigating stress and improving coping skills [29]. Participants also identified a need for more flexibility in the intervention delivery and a desire for more informal support and ongoing contact after birth that psychologists were unable to provide [29].

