### Criteria for discontinuing or modifying allocated interventions {11b}

Following randomization, peer counsellors will attempt to reach participants via telephone, text, and email (as necessary). Participants who do not respond after 8–10 attempts to establish contact will no longer receive treatment but will remain in the study. If any response is provided to attempted contact, peer counsellors will continue to reach out to schedule remote-counselling sessions, unless the participant expresses a desire to withdraw from the study or they reach the end of pregnancy. Participants will also no longer receive treatment if they do not complete the intervention before the end of pregnancy. If acute suicidality is indicated, either through the study questionnaires or in weekly remote-counselling sessions, the participant will no longer receive treatment and the clinical team will provide a referral to the appropriate care resources using the established referral pathway.

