### Strategies to improve adherence to interventions {11c}

Peer counsellors will schedule weekly remote-counselling sessions in accordance with the participants’ availability and will remind participants of upcoming sessions about 24 h before the session or as decided with the participant. Sections of the self-administered workbook will be assigned for each session and participants will be reminded of the assigned sections. In the case that a participant has not completed the assigned materials before the session, the peer counsellor will guide the participant through the workbook content during the session time. In each session, peer counsellors will inquire as to the amount of assigned materials completed before session and any barriers to completing the BA materials. To ensure peer counsellor adherence to the protocol, peer counsellors will also attend a weekly 90-min clinical supervision with a member of the clinical team.

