### Outcomes {12}

The primary outcome is gestational age at birth in days, measured using electronic health records, obtained for the P3 Cohort.

Secondary outcomes are:Change in symptoms of depression across T1 and T2 between the treatment and control groups, measured as overall score on the EPDS; and lower odds of scoring 13 or greater on the EPDS at T2, T3, and T4.Change in symptoms of anxiety across all timepoints (measured by the PROMIS – anxiety 7a-item short form self-report questionnaire [41])

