### Participant timeline {13}

The overall participant timeline is illustrated in Fig. 1.

Week 1 (T1): Participants of the P3 Cohort study will complete a baseline assessment during pregnancy (less than 27 weeks GA). Individuals who are eligible for this study will be identified and will be contacted by a member of the study team to be invited to participate. The study team member will outline the study protocols and obtain informed consent.

Week 2: Participants will be randomly assigned, using computer-generated block randomization, into the intervention group or the standard of care control group.

Weeks 3–6: Participants randomized to the intervention group will complete the BA counselling sessions with a peer counsellor via telephone, in addition to regular informal peer-support contact. Participants in the control group will continue to receive standard of care.

Week 8–10 (T2): At 34 to 36 weeks gestation, after the completion of the intervention, all participants will be invited to complete an electronic P3 Cohort questionnaire.

Post-due-date (up to 6 weeks postpartum): After childbirth, information about gestational age at delivery will be collected for the P3 cohort via linkage to the participant medical record. Participants will continue to have informal peer-support (social support, advice, information sharing) contact with peer counsellors via text and telephone, up to 6 weeks postpartum.

Five to 6 months postpartum (T3): All participants will be invited to complete an electronic questionnaire as part of their participation in the P3 Cohort.

Eleven to 12 months postpartum (T4): All participants will be invited to complete an electronic questionnaire as part of their participation in the P3 Cohort.

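### The completers-only sensitivity analysis selects on gestational age in the intervention arm alone, so against all controls it favours longer gestation even with no treatment effect

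*Protocol article*

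**What the plan says.** All places are in the protocol article.

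- Outcomes {12}: "The primary outcome is gestational age at birth in days".
- Non-adherence and missing data {20c}, main analysis: "Analysis will be completed in accordance with an intention-to-treat (ITT) model and will therefore include all participants, regardless of protocol adherence or missing data".
- The same section then adds: "A secondary sensitivity analysis will also be conducted including only those who completed the intervention with adherence to the treatment protocol". It names no landmark, no matching restriction on controls and no complier-effect method.
- Discontinuing interventions {11b}: "Participants will also no longer receive treatment if they do not complete the intervention before the end of pregnancy".
- Inclusion and exclusion criteria: entry is limited to less than 27 weeks, with the stated purpose "to enable completion of the intervention prior to delivery, and allow us to capture the vast majority of preterm deliveries". No lower limit is given.
- Schedule: section {11a} says "Treatment will involve an average of 6–8 structured counselling sessions", section {11c} says "Peer counsellors will schedule weekly remote-counselling sessions", and the timeline {13} says "Weeks 3–6: Participants randomized to the intervention group will complete the BA counselling sessions".
- The control group receives standard of care and has no intervention to complete.

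**The concern.** To count as a completer, a participant must still be pregnant when her last session takes place. Whoever delivers before that point is dropped, and the reason is the outcome under study. This is immortal-time bias: a completer cannot, by definition, have delivered between entry and completion, while a control can deliver on any day and still count.

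A sensitivity analysis should show whether the main result withstands other assumptions. On the primary outcome this one is pushed toward benefit. A null intention-to-treat result could stand beside an apparently favourable result in adherent participants, or a small real effect could appear to grow with adherence when only the selection has changed.

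**Working it through.** **The plan's own figures.** The article gives no figure for the completer analysis. Its sample size reproduces as 214 × 1.15 = 246.1, reported as 246. The 3-day target is used here only as a yardstick. Its power statement cannot be checked because no SD is given; with 123 per group it implies an SD of 3 / [(1.960 + 0.842) × √(2/123)] ≈ 8.4 days.

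**Direction.** Let q be the share of the intervention arm that delivers before completing, K the mean gestation of those kept and E that of those excluded. With no treatment effect, controls have the same mean as the whole intervention arm:

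- mean of all = (1 − q)K + qE
- completers minus controls = K − mean of all = q(K − E)

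If completion date is otherwise unrelated to delivery date, the chance of being kept rises with gestational length. So K exceeds E and the difference is positive whenever q is above zero. No outside data are needed for this step.

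**Size: assumptions.** None of these is fixed by the article.

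- Preterm rate 8–15%.
- Term births: normal, mean 276 days, SD 7.5, cut off below 259 days. Preterm births: 259 days minus a gamma variable (shape 1.2, scale 12 days).
- Entry spread evenly over 12–27, 20–27 or 24–27 weeks.
- Delivery is the only reason for not completing.
- Quick completion: 6 weeks after entry, following the timeline {13}.
- Slow completion: entry + 2 weeks + 6–8 weekly sessions ({11a}, {11c}) + 0–3 weeks of assumed slippage, which is 8–13 weeks after entry.

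**Size: results.** Spurious gain in mean gestational age, completers minus all controls, with no true effect. Each range runs from 8% to 15% preterm birth.

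| Entry window | Quick completion | Slow completion |
|---|---|---|
| 12–27 weeks | 0.08–0.15 days | 0.6–1.0 days |
| 20–27 weeks | 0.17–0.31 days | 1.2–2.1 days |
| 24–27 weeks | 0.31–0.56 days | 2.0–3.5 days |

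Against the target, 0.08 / 3 is about 3% and 3.5 / 3 about 117%. The share of preterm births that stays in the completer set runs from 98% (quick, widest window) to 35% (slow, latest window).

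**Check with a different distribution.** Term births were about normal (277, 8.5 days), and preterm births an exponential tail with mean 16 days below 37 weeks. Completion 6–10 weeks after entry gave 0.1–3.2 days. Completion fixed at 34, 35 or 36 weeks gave 1.1–2.0 days at 8% preterm, 1.6–3.0 at 12% and 1.9–3.7 at 15%.

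Take 12% preterm and completion at 34 weeks. Only 3.09% of the arm is excluded and the bias is 1.56 days, so K − E = 1.56 / 0.0309 ≈ 50 days. A few very early births are enough. Measured preterm birth falls from 11.9% to 9.1% in the same scenario.

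Intention to treat, or the same still-pregnant-at-a-landmark restriction in both arms, gives zero in expectation.

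**The case against.** Several points on the other side are fair, and most of them limit the size.

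- A reader might infer that anyone who delivers early cannot complete. The article does not support that. The entry limit exists so that the intervention can finish before delivery, and an early entrant can complete and still deliver preterm. Only delivery before completion excludes. This stands.
- The timeline ends the sessions at study week 6. On that schedule the bias is at most about 0.6 days. This stands, but 6–8 weekly sessions do not fit into study weeks 3–6, so the range has to cover both readings.
- The upper end needs 15% preterm birth, entry only at 24–27 weeks, and slippage, none of which is in the article. This stands.
- The article does not say how controls enter. A reader might infer that the analysis has no comparator at all, but that is detail a condensed article may leave to the full plan. The ordinary reading is completers against controls, and the size above is conditional on it.
- The planned primary method is time-to-event, while the figures are differences in means. They show scale and do not quantify bias in a hazard ratio. The direction carries over, because completers contribute event-free time before completion by construction.
- The analysis is secondary, and no hypothesis or sample size rests on it. This stands and sets the severity.

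What does not stand is that this is only missing detail. The selection rule is stated, and on the ordinary reading it gives a wrong answer for the primary outcome.

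**Conclusion.** The point holds. The completers-only set conditions on gestational age in one arm, and comparing it with all controls favours longer gestation under no effect. The direction follows from sections {11b}, {12} and {20c}. The size, about 0.1 to 3.5 days in means against a 3-day target, rests on the assumed preterm rate, birth distribution, entry window and completion time.

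A reader might go further and infer that the trial's main result is compromised, or that the bias is routinely near 3 days. The documents support neither: the intention-to-treat analysis keeps everyone and is untouched by this, and with early entry and quick completion the bias is a small fraction of a day. This is a should-fix.

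**What to change.** For gestational age, replace the completers-only analysis with one that does not condition on pregnancy length in one arm. Any one of these would do:

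1. **Landmark.** Apply one pre-specified gestational-age landmark (still pregnant at week X) to both arms, and state that the result describes only pregnancies that reach it.
2. **Time-varying exposure.** In the planned time-to-event model, count a participant as completed only from her completion date. This removes the immortal-time bias but not confounding by who adheres.
3. **Complier-average effect.** Keep all randomised participants, use randomisation as the instrument, and choose an exposure that delivery does not cap, such as having started treatment (yes/no). A session count is unsuitable because early delivery shortens it. On a hazard-ratio scale this needs special methods.

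If the completer analysis is kept, say how controls enter, and state that it is biased toward longer gestation and does not support the primary claim. Separately, sections {11a}, {11c} and {13} should be reconciled on the length of the session period, since the size of the bias depends on it.

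Cost: a change of wording, a little more analysis work and some loss of precision. No new participants are needed. Option 2 uses session dates, and option 3 only whether treatment was started.

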### Plans to give access to the full protocol, participant level-data and statistical code {31c}

[name] will be the primary custodian of the data. All de-identified data and analysis code will be made available upon reasonable request following the completion of all primary, secondary and exploratory analyses by the study team.

The Cumming School of Medicine offers Randomised Trial supports including database management and compliance monitoring. Through memberships in the Alberta Children’s Hospital Research Institute, the Hotchkiss Brain Institute, and the O’Brien Institute for Public Health, the team has access to graduate training studentships, student project funding, methods consultation, communications support, interdisciplinary research rounds, support for online data collection and management, knowledge translation support, and yearly research symposia. UCalgary provides Equity Diversity and Inclusion (EDI) facilitation for hiring and trainee selection, and departmental meeting facilities, administrative support, and research nurses to aid with recruitment.

### Composition of the data monitoring committee, its role and reporting structure {21a}

Data will be monitored by co-PIs [name] and [name], with oversight from the larger P3 Cohort leads ([name], [name], [name]). PIs will meet regularly with research assistants to monitor data integrity, participant follow-up and attrition.

### Adverse event reporting and harms {22}

Peer counsellors will receive regular, weekly clinical supervision from a team of qualified clinical psychology supervisors, with senior oversight from PI [name]. Supervision will ensure referral of participants to appropriate care if the need arises and provide guidance for peer counsellors in managing participant concerns, circumstances and clinical needs. Participants will be informed to contact research assistants and/or co-PIs to report potential adverse events, which will then be reported in accordance with University of Calgary Conjoint Health Research Ethics Board (CHREB) guidelines.

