
**Fig. 1 Fig1:**
[figure not shown]
SPIRIT schedule of enrolment, intervention, and assessments

Once the peer counsellors have obtained their competency approval, they will be paired with a single randomized participant and will establish contact with them to initiate and administer the intervention. The peer-delivered intervention will be conducted through Zoom for Healthcare and telephone contact between the peer counsellors and participants. Zoom sessions will be recorded for the purposes of supervision, which is intended for both clinical oversight and continued refinement of peer counsellor’s competencies and therapeutic skillset. In addition to between 6 and 8 structured BA therapy sessions, peer counsellors will also provide informal and unstructured peer support via telephone and/or text. This will include both participant-initiated and peer counsellor-initiated check-ins, sharing of information, and peer guidance. The peer support component will be available to participants up to 6 weeks postpartum, for a total possible length of time of 12 weeks. Peer counsellors may opt to be paired with subsequent participants following completion of the intervention and peer support components. All peer counsellors will receive weekly mandatory clinical supervision via 60-min remote group meetings provided by a clinical psychology graduate trainee, and additional individual supervision meetings as needed, to ensure patient safety and treatment fidelity, and peer counsellor adherence to the protocol. All trainee peer supervisors will be supervised by a registered clinical psychologist through regular virtual group supervision and one-on-one supervision as needed. Fidelity will be addressed with the weekly supervision sessions with the peer counsellors. During the weekly supervision sessions, it will be emphasized that external resources outside of what we provide them cannot be recommended. We will also request that peer counsellors keep an informal record of peer support that they deliver, which will be reviewed during supervision. Peer counsellors will be offered a stipend of $250 for each intervention cycle administered to a single participant, to acknowledge their time and contribution to the study. Following their final intervention cycle in the current study, peers will be invited to complete a qualitative individual in-depth interview, conducted by a trained research assistant under the supervision of the PIs ([name], [name]). Interviews will elicit reflective conversation around the experiences of peers in delivering the intervention, and any perceived positive or negative impacts the experience may have on their well-being. We will also explore their thoughts and opinions on strengths and weaknesses of the intervention and its delivery (including the training experience) and whether they have suggestions for improvement in the future.

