
The control group will receive standard of care, including receiving routine obstetric care and referral to community mental health resources, and will also complete all study assessments.

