#### Secondary outcomes

*Symptoms of depression* will be measured using the Edinburgh Postnatal Depression Scale (EPDS). The EPDS is a 10-item questionnaire that will be administered at less than 27 weeks gestation (T1), 34–36 weeks’ gestation (T2, post-intervention), 5–6 months postpartum (T3), and 11–12 months postpartum (T4). The EPDS has been validated to measure major depressive disorder against diagnostic interviews in pregnant individuals and is a valid and reliable measure of symptoms of depression during the perinatal period [34, 35, 43].

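### Volunteered and session-disclosed adverse events would probably be captured more completely in the intervention arm, so raw counts of them by arm should not be compared

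*Protocol article*

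**What the plan says.** Adverse event reporting and harms {22} states two things. The first is supervision: "Peer counsellors will receive regular, weekly clinical supervision from a team of qualified clinical psychology supervisors", with the purpose that "Supervision will ensure referral of participants to appropriate care if the need arises", plus guidance for the counsellors. The second is the reporting route: "Participants will be informed to contact research assistants and/or co-PIs to report potential adverse events". Reports then go to the ethics board under its guidelines. The section names no scheduled enquiry about adverse events.

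Contact with the study differs by arm.

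- **Intervention arm.** Strategies to improve adherence {11c}: "Peer counsellors will schedule weekly remote-counselling sessions in accordance with the participants’ availability". Intervention description {11a}: "In addition to between 6 and 8 structured BA therapy sessions, peer counsellors will also provide informal and unstructured peer support via telephone and/or text". Such support includes check-ins started by the counsellor and runs to 6 weeks postpartum. The Zoom sessions are recorded for supervision. Counsellors are trained to start a referral pathway when suicidality, intent to harm or an emergency comes to light.
- **Control arm.** Intervention description {11a}: "The control group will receive standard of care, including receiving routine obstetric care and referral to community mental health resources". Controls also complete all the study assessments.

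Criteria for discontinuing {11b} names two ways in which acute suicidality may be indicated: the study questionnaires and the weekly sessions. Only the first exists for controls.

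**The concern.** In a two-arm trial, a count of adverse events by arm is informative only if events have a similar chance of being found in each arm. Here the general route is spontaneous report, and one arm has an additional channel: a trained listener in weekly contact whose cases are reviewed in supervision. A crisis between questionnaires may come up in a session, whereas a control participant would have to contact the study unprompted.

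If events of this kind are later tabulated by arm, an apparent excess under the intervention could arise from detection alone. Equally, a real excess could be dismissed as a detection artefact. Unequal collection cannot be repaired at the analysis stage, so the time to address it is before data are collected.

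**Working it through.** The plan states no adverse-event rate, detection rate or harms comparison, so it has no figure to reproduce. The check sets the detection routes side by side, counts contacts, and then shows by illustration how far the result depends on unknown inputs.

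**Step 1. Routes by arm**

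| Source | Intervention | Control | Section |
|---|---|---|---|
| Volunteered report to staff | yes | yes | {22} |
| 6 to 8 weekly sessions | yes | no | {11a}, {11c} |
| Check-ins and text support to 6 weeks postpartum | yes | no | {11a} |
| Suicidality indicated in sessions | yes | no | {11b} |
| Suicidality indicated on questionnaires | yes | yes | {11b} |
| EPDS and PROMIS anxiety at T1 to T4 | yes | yes | {18a} |
| NICU admission, length of stay, readmission from linked records | yes | yes | {18a} |

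The first row is the same on paper, but a participant in weekly contact with the study has more prompts to report. The next three rows are open to one arm only. The last three are the same in both.

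**Step 2. Scheduled contacts after randomisation**

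T1 precedes randomisation (Participant timeline {13}), so three questionnaires follow it: T2, T3 and T4.

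- Intervention: 6 + 3 = 9 to 8 + 3 = 11, plus informal contact.
- Control: 3.

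Controls have no scheduled study contact between randomisation and T2, and none between T2 at 34–36 weeks and T3 at 5–6 months postpartum. The second gap spans delivery and the early postpartum, when the intervention arm still has counsellor support up to 6 weeks. The sessions are opportunities for disclosure; the article does not describe them as adverse-event enquiries.

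**Step 3. Illustration with assumed rates**

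Let the true risk p be equal in both arms, with detection probabilities d_I and d_C. The recorded risks are p × d_I and p × d_C, so the apparent risk ratio is d_I / d_C whatever p is. Assume p = 10%, d_I = 90% and 123 per arm (Sequence generation {16a}). The last column is the normal-approximation chance that a two-sided 5% test of two proportions shows a significant excess in the intervention arm.

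| Assumed d_C | Recorded risks | Apparent ratio | Chance of spurious significant excess |
|---|---|---|---|
| 90% | 9% vs 9% | 1.00 | 2.5% (nominal) |
| 70% | 9% vs 7% | 1.29 | 8% |
| 50% | 9% vs 5% | 1.80 | 23% |
| 30% | 9% vs 3% | 3.00 | 51% |

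At p = 20% the last three chances become 13%, 44% and 83%. Every ratio simply restates the detection rates put in. The table shows the direction and the sensitivity; it is not an estimate for this trial.

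**The case against.** The strongest reply has four parts.

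- **Much is collected alike.** A reader might infer that harms cannot be compared between arms at all, or that worsening depression will look more frequent under the intervention. Neither follows. The EPDS and the PROMIS anxiety form are given to both arms at T1 to T4, and EPDS score and EPDS 13 or greater are secondary outcomes compared between arms. Questionnaire-indicated suicidality and linked-record events also come from common sources. Session contact does not change how any of these is counted. This part stands, and it confines the point to volunteered and session-disclosed events.
- **No adverse-event comparison is planned.** The outcome and analysis sections list none, and {22} describes safety handling. This stands as well: the plan does not commit to a biased comparison. The point is a safeguard for when events are read by arm, as they naturally will be.
- **Supervision is not described as a recording route.** Its stated roles are referral and guidance. That session disclosures would be logged as adverse events is an inference. It is a reasonable one, since supervision is described under the harms heading, but it remains an inference.
- **The article is condensed.** Event definitions, forms and procedures may be in the full protocol, which is not shown, and their absence is no fault. A reader should not infer that the trial has no solicited collection. The point rests on what the article does state: a spontaneous general route in {22}, and in {11b} a session route to suicidality that controls lack.

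A further tempting step is to say that the trial cannot then support its low-risk premise. Interim analyses {21b} gives low risk as one reason for having no interim analysis. It is not put forward as a conclusion to be drawn from adverse-event counts.

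**Conclusion.** The concern holds in a limited form. Volunteered and session-disclosed events, above all crises between questionnaires, would probably be captured more completely in the intervention arm. Raw counts of them by arm would then lean towards an apparent excess there.

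The direction rests on two assumptions: that disclosures in sessions reach the adverse-event record, and that frequent contact makes disclosure more likely. The size cannot be derived from the article. A claim that events are counted far more completely in one arm, or that the spurious ratio has a particular value, would rest on assumed detection rates alone.

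EPDS and PROMIS scores, questionnaire-indicated suicidality and linked-record events remain comparable. The primary outcome, gestational age from linked records, is unaffected. This is a worthwhile, inexpensive improvement and does not call the main comparison into question.

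**What to change.** 1. Add one adverse-event question, worded identically for both arms, to the existing T2, T3 and T4 questionnaires.
2. State that any between-arm statement on harms will use only sources common to both arms: that question, EPDS worsening from T1, questionnaire-indicated suicidality, and linked-record events.
3. List events disclosed in sessions or volunteered to staff in a separate table, marked as not comparable between arms.

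If the full protocol already contains a solicited enquiry common to both arms, a sentence in {22} saying so would replace the first step. None of this alters the referral pathway or the care of any participant.

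The cost is one question on three existing electronic questionnaires and one short extra table, with slight added participant burden and more events to process. The change reduces the imbalance without removing every source of it: participants know their allocation, and a self-reported answer depends on the questionnaire being returned.
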